#### Fecal Sample Collection

Participants provided fecal samples for the analysis of gastrointestinal microbial composition using the Easy Sampler stool collection kit (EasySampler, GP medical devices, Denmark), as per the manufacturer’s instructions. The samples were immediately stored at −80°C, until subsequent analysis.

#### Ectopic Lipid Content

After the steady-state exercise test, the participants consumed a standardized meal (Energy: 2553 kJ; protein: 20.9 g; carbohydrates: 83.0 g; fat: 22.2 g). Hepatic, pancreatic, and skeletal muscle (tibialis anterior and soleus) lipid content were then measured on a 3-Tesla Skyra wholebody human MRI scanner (Siemens, Erlangen). Sequence protocols for fat assessments included MRI using two-point Dixon fat-water separation (Dixon-VIBE) and T1-VIBE with and without fat saturation, and finally, MRS with PRESS technique.

Postprocessing of MRI data for Dixon and T1-VIBE was performed in MATLAB R2009a (MathWorks Inc, Natick, MA, USA). The MRS voxel locations were coregistered to T1-VIBE images (with and without fat suppression) and Dixon images (fat and water images) to compute the fat fraction. The signal fat-fraction was calculated as the signal without fat suppression minus signal with fat suppression divided by signal without fat suppression for the T1-VIBE method [51]. The signal fat fraction obtained by the Dixon method was calculated by combining images obtained from the water and fat phases, as the fat fraction divided by the fat plus water fractions [52]. MRS data were quantified using LCModel (version 6.3-1J) **.** The MRS method was used to decompose the lipid signals into several components, each one representing different parts of the lipid metabolite molecules. The lipid signals were reported relative to the water signal.

#### Skeletal Muscle and Adipose Tissue Biopsies

After a 4- to 6- hour fast and at least 48 hours after exercise, fat and muscle samples were collected. Fat samples were obtained from the gluteal and abdominal SAT depots using a mini-liposuction technique [16]. After local anesthesia with Lignocaine hydrochloride (2%, Intramed, Port Elizabeth, South Africa), a small incision was made into the region of interest and 200 mL of normal saline with 20 mL 2% Lignocaine (Intramed) was infused using an infiltration cannula (Lamis 14 ga x 15 cm, Byron Medical Inc., Tucson, AZ, USA). An aspiration cannula (Coleman, 12 ga x 15 cm, Byron Medical Inc.) attached to a 10-mL syringe was used to aspirate fat. Using this procedure, abdominal samples were obtained from directly above the umbilicus, and gluteal samples were obtained from the right upper outer quadrant. Approximately 2 cm^3^ to 3 cm^3^ of fat was extracted from each site and washed 3 times with normal saline or until no blood was visible. A subsample of the adipose tissue was placed in ice-cold BIOPS for immediate analysis of mitochondrial respiration. The remaining adipose samples were placed into vials and frozen immediately in liquid nitrogen (N_2_) and stored at −80°C for the analysis of gene and protein expression, and fatty acid composition. After local anesthesia (2%, Intramed), a skeletal muscle biopsy was taken from the *M vastus lateralis* muscle using a 5-mm Bergstrom needle according to the needle biopsy technique of Bergstrom [53]. A subsample was placed in ice-cold BIOPS, for immediate analysis of mitochondrial respiration. The remaining samples were immediately frozen in liquid N_2_ and stored at −80°C for subsequent analysis of gene and protein expression, as well as metabolomics and lipidomics.

### Monthly Monitoring

#### Physical Activity, Sedentary Behavior, and Sleep

Physical activity and sleep quality and quantity were measured using accelerometry (ActiGraph GTX3+, ActiGraph LLC, Pensacola, Florida), and sedentary behavior was measured using activPAL (activPAL3c, PAL Technologies Ltd, Glasgow, UK) at preintervention, week 4, week 8, and postintervention. The ActiGraph was initialized to record data in 60-second epochs and was set to measure motion in all 3 axes, with the inclinometer function activated. The ActiGraph was worn on the right hip with a lightweight belt, and participants were instructed to wear it for 24 hours a day over a 7-day period, except when swimming, bathing, and showering. Participants were instructed to complete a sleep diary to capture awake and sleep times. Physical activity and sleep data were captured and analyzed using the ActiLife Software Version 6 (ActiLife software; Pensacola, FL, USA). A minimum of 4 days of wear time, with 600 min per day of wake time was required for data analysis. The 4 days of wear needed to be inclusive of 3 weekdays and 1 weekend day. For the exercise group, at least one of the weekdays needed to be an “exercise day.” Nonwear time was defined as 60 continuous minutes of no counts (zeros) [54]. Vector magnitude cut-points were used for analysis [55,56]. The vector magnitude represents the summed value of all 3 axes measured from the ActiGraph, calculated as the square root of the total sum of each axis, squared (X^2^+Y^2^+Z^2^), then square rooted [57]. Counts/minute between 200 and 2689 represents light intensity physical activity, 2690 to 6166 represents moderate intensity physical activity, 6167 to 9642 represents hard intensity physical activity, and >9643 counts per minute represents very hard intensity physical activity. Data were analyzed for any physical activity occurring in 1-min and 10-min bouts/intervals. Within each 10-min bout, 1- or 2-min of “dropped” counts were allowed, thereby excluding bouts of activity where a drop-in count is greater than 2 min (within the 10-min period) occurred. Sleep data were analyzed for sleep latency, total sleep time, wake after sleep onset, and sleep efficiency. Participants completed a sleep diary that was used to mark wake and sleep hours, which was further verified based on movement measured by the activPAL.

The activPAL was attached to the midanterior right thigh using a waterproof sleeve and dressing and worn concurrently with the ActiGraph, without removal of the device, even during bathing or swimming. All data were downloaded using the activPAL software (PAL Technologies, version 7.2.32, Glasgow, UK), and event files were used to create second-level files to show time spent in sitting (or lying), standing, stepping, sit-to-stand transition, and stand-to-sit transition.

#### Dietary Intake

At the same time points as the physical activity data collection, dietary intake was estimated using a 24-hour recall and a 3-day dietary record, including 2 weekdays and 1 weekend day. In addition, a food frequency questionnaire was administered before and following the intervention. Nutrient intake and food group analysis were calculated using the South African Food Composition Database System (SAFOOD, the South African Food Composition Database, South African Medical Research Council, Cape Town, South Africa).

#### Perceptions of the Exercise Intervention

Focus group discussions (FGDs) and in-depth interviews were used to explore the perceptions participants had of the exercise intervention. A multiple-category qualitative research design was applied in this study [58]. This type of design includes conducting focus groups with different types of participants either sequentially or simultaneously [58]. This approach ensures a comparison from one group to another within a category and/or from one category to another category [58].

The focus group interview schedule included questions such as “What are some of the things that influenced your attendance to the exercise sessions?”, whereas the in-depth interviews included 1 main open ended question aimed at obtaining the participants’ experience of the exercise sessions (Multimedia Appendix 1). The latter were conducted after the FGD and participants who were the most vocal during the group discussions were purposively selected for the in-depth interviews.

Four FGDs were conducted (3-5 participants per group), including exercise participants, and control participants who had chosen to participate in the exercise sessions upon completion of the 12-week intervention. The group discussions were moderated by a trained facilitator, fluent in isiXhosa, which is the language predominantly spoken by the participants. The audio recording of the FGDs was translated and transcribed by a trained professional. Immediately after completion of the FGDs, the researcher and moderator identified participants to be invited to participate in the in-depth interviews. A total of 5 in-depth interviews were conducted **.** Thematic analysis was used to determine the salient themes that emerged during the FGDs using Atlas.ti Qualitative Data Analysis Software (Scientific Software Development GmbH, Berlin, Germany) [59].

### Biochemical Analysis

#### Glucose, Insulin, C-Peptide, and Lipid Profile

Plasma glucose and serum lipids concentrations were determined using a colorimetric assay (Randox, Gauteng, South Africa) and serum insulin, C-peptide were measured using immunochemiluminometric assays (IMMULITE 1000 immunoassay system, Siemens Healthcare, Midrand, South Africa).

#### Serum Inflammatory and Oxidative Stress Markers

Inflammatory cytokines, including interleukin (IL)6, IL1R, IL8, IL10, monocyte chemotactic protein (MCP)1, IL15, interferon (IFN) gamma, and tumor necrosis factor (TNF) alpha, were measured using Milliplex MAP MAG Human Cytokine kit (Merck, Johannesburg, South Africa) and xMAP technology (Luminex, Austin, Texas) according to the manufacturer’s instruction. Serum concentrations of leptin and high molecular weight (HMW) adiponectin (EMD Millipore Corporation, St Charles, Missouri, USA) were analyzed using commercially available ELISA kits according to the manufacturer’s protocols. High-sensitive C-reactive protein (CRP) was measured by an immunochemiluminometric assay (IMMULITE 1000 immunoassay system, Siemens Healthcare, Midrand, South Africa). Lipid peroxidation was assessed by measuring the concentration of thiobarbituric acid reactive substance (TBARS); antioxidant capacity was assessed by measuring oxygen radical capacity absorbance (ORAC), as well as catalase and superoxide dismutase (SOD) activities as described previously [60].

#### Red Blood Cell and Adipose Tissue Fatty Acid Composition

Total lipids of red blood cell aliquots (RBC; 300 µL) and adipose tissue portions (100 mg) were extracted (2:1; v:v; chloroform:methanol containing 0.01% butylated hydroxytoluene) by using a modification of the Folch et al method [61,62]. Red blood cell total phospholipid fatty-acid (FA) and adipose tissue total FA percentage composition were determined by gas-liquid chromatography as previously described [62]. Pairwise analysis of gluteal and abdominal samples was performed including the pre- and postsamples of a participant in the same batch on the same day. Product to precursor FA ratios were used as a proxy to reflect delta-6- and delta-5-desturase enzyme activity [63].

#### Comprehensive Metabolite Profiling of the Serum and Muscle Metabolome

For the metabolite analyses, a combined platform of liquid (LC-QTOF-MS) and gas (GCTOF-MS lipids) chromatography coupled to mass spectrometry, in both positive and negative ionization modes will be used. This approach will enable a comprehensive coverage of serum and muscle metabolites with different chemical properties. All sample preparation and analyses will be performed according to a run order design to circumvent methodological biases that may interfere with results interpretation [64]. For example, samples from the same individual are prepared and analyzed in close connection while keeping the internal sample order randomized. Analytical batches will be balanced in terms of treatment group and quality control (QC) samples (ie, pooled from all samples) will be analyzed continuously.

Serum samples will be prepared according to A et al [65], using a 90/10, v/v methanol:water extraction including internal standards for metabolomics; and a 70/30, v/v chloroform:methanol extraction for lipidomics [66].

On an average, we will detect 2000 to 3000 peaks or more, and annotation/identifications will be done via the use of publically available library, in combination with *in house* library at the Swedish Metabolomics Centre (SMC). For targeted analyses and validation of findings, we will use triple quadrupole mass spectrometry techniques, such as LC-QqQ-MSMS or GC-QqQ-MSMS together with LC-TQMSMS and GC-TQMSMS in MRM-mode. Absolute quantification of specific compounds will be achieved by using calibration curves calculated from stable isotope labeled internal standards.

### Serum HDL- and LDL-Cholesterol Subclasses and HDL Functionality

HDL was isolated from aliquots of serum using density shift ultracentrifugation as described previously [67,68]. HDL anti-inflammatory function was measured by assessing expression levels of vascular cell adhesion molecule (VCAM) human umbilical vein endothelial cells (HUVEC) treated with participant HDL and stimulated with murine TNF-α, as described previously [67]. HDL antioxidant function was quantified by measuring serum paraoxonase-1 (PON1) activity as described previously [67]. HDL-induced reverse cholesterol efflux was quantified using a modified method [69]. Briefly, RAW264.7 cells ([name], Nelson Mandela Metropolitan University), were labeled with [^3^H] cholesterol in a medium containing acyl-CoA cholesterol acyltransferase (ACAT) inhibitor. Isolated participant HDL was then added and cholesterol efflux was carried out for 4 hours. Reverse cholesterol efflux capacity was calculated as label present in the cell media relative to the untreated control. HDL anti-thrombotic function was quantified by measuring serum platelet activating factor acetylhydrolase (PAF-AH) activity using the PAF Acetylhydrolase Assay Kit (Cayman Chemical, 760901). Serum HDL and LDL subclass were determined using the Lipoprint HDL and LDL systems (Quantimetrix, Redondo Beach, CA) as described previously [67,70].

### Skeletal Muscle and Adipose Tissue Gene and Protein Expression

RNA was extracted from adipose tissue and skeletal muscle samples using RNeasy Mini lipid kit (Qiagen Ltd, Germantown, MD, USA) and mirVana miRNA Isolation kit (Invitrogen, Life technologies, Carlsbad, CA, USA), respectively. Skeletal muscle RNA was DNAse treated using DNA-free Kit (Invitrogen, Life technologies, Carlsbad, CA, USA). RNA was reverse transcribed to cDNA using the High-Capacity cDNA Reverse Transcription Kit with RNase inhibitors (Applied Biosystems Foster City, CA, USA).

For the adipose tissue, RT-PCR will be performed in triplicate using Applied Biosystems QuantStudioTM 3 Real-Time PCR system with predesigned Taqman assays from Applied Biosystems (Warrington, UK) (see Multimedia Appendix 2). The genes of interest will be measured and presented as the ratio of abundance of the gene of interest: mean of abundance of the relevant housekeeping genes (LRP10 and RPLPO). Protein expression, and phosphorylation status, for genes of interest will be analyzed using ELISA and/or Western Blot analyses.

For skeletal muscle, a gene array was conducted using Human Affymetrix Cartridge Clariom S Platform (Affymetrix, Santa Clara, CA, USA) and analyzed with Affymetrix Expression Console using the SST-RMA method. Unlogged signals were compared using a 2-tailed paired Student *t*-test. The q-values (false discovery rates) were calculated by the R/Bio-conductor function and set at q<.05. Target and novel pathways will be investigated using the gene array data, and genes of interest and associated proteins will be further validated using RT-PCR and western blots analyses, respectively.

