### Statistics

#### Sample Size Determination

Sample size determination was based on our primary outcome using the study of Nordby et al [80], with a significance level of *P*<.05 and power of 80%. On the basis of the change in normalized glucose clearance (measured using a euglycemic hyperinsulinemic clamp) from pre- to postintervention (12-week aerobic training) compared with the nontrained control group (8.2 [SD 5.9] vs −1.8 [SD 6.2] mL/kg/min FFM/nmoL/L insulin, respectively), 6 participants per group would be required to detect a significant difference between groups. These numbers correspond to those of Ortega et al [81] who compared glucose tolerance tests to detect the insulin sensitizing effects of a bout of continuous exercise and reported that 6 participants would be required to detect a change in insulin sensitivity when using a FSIGT. In order to account for the secondary outcomes, using changes in skeletal muscle glucose transporter (GLUT)4 in response to a 12-week training program as the proxy (0.65 [SD 0.69] vs 0.01 [SD 0.69] AU for training vs control group), 18 women would be required to detect a difference between groups [81]. On the basis of these calculations, and a dropout rate of 10% (2/20), 20 participants per group were selected.

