#### Proposed Statistics

Results will be presented as means (SD), or medians and interquartile ranges for non-normally distributed data. Data will be normalized by log transformation if required. Repeated measures ANOVA will be used to compare differences in the change of outcome variables between the control and exercise groups in response to the exercise/control intervention. Pearson and/or Spearman correlations will be used to examine associations between changes in primary and secondary outcome variables. Data will be analyzed using StataSE (version 14, StatCorp, Texas, USA) and IBM SPSS Statistics 24 (Version 24.0, Armonk, NY, USA).

Comprehensive metabolite profiling data will be evaluated via a combination of multivariate analysis methods and univariate statistics, that is, Principal Component Analysis (PCA), Orthogonal Partial Least Squares (OPLS), and its extensions [64]. In addition, we will perform an extensive validation to determine the model significances, using both internal, ANOVA on the cross-validated model patterns, and external validation, independent sample prediction. Model scores (subject level) will be used to visualize and interpret the differences in metabolic response between predefined patient groups or subgroups, or of individual patients responding differently to the interventions. Model loadings (variable level) combined with univariate *P* values will be used as the base for mechanistic interpretation and to highlight significant metabolites or metabolite patterns.

For bacterial community analysis, basic statistical tests will be performed using QIIME [77] and R software will be used for advanced statistical analysis. Beta-diversity will be evaluated by calculation of weighted and unweighted Unifrac distances. The Shannon and Simpson diversity indices will be employed to study alpha-diversity. The relationship between the composition of the fecal bacteria and exposure variables will be determined using weighted generalized ridge regression methods [82] and the lasso [83]. We will use Dirichlet multinomial models or ecological approaches such as multi-species occupancy models to evaluate interactions and shift in fecal bacterial communities over time [84,85].

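### The only test given for the muscle gene array is a paired t test on unlogged signals, which does not use the control arm as comparator and conflicts with the trial's between-arm rule

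*Protocol article*

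**What the plan says.** The section Skeletal Muscle and Adipose Tissue Gene and Protein Expression says the muscle array was "analyzed with Affymetrix Expression Console using the SST-RMA method". It continues: "Unlogged signals were compared using a 2-tailed paired Student" *t* test, and "The q-values (false discovery rates) were calculated by the R/Bio-conductor function and set at q<.05". Genes of interest and their proteins then go forward to RT-PCR and Western blot. The section does not define the pairs, name the arm or arms tested, or say whether control biopsies were arrayed.

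Proposed Statistics gives the general rule: "Repeated measures ANOVA will be used to compare differences in the change of outcome variables between the control and exercise groups". On scale it says "Data will be normalized by log transformation if required". It adds specific plans for the metabolite and microbiome data, but none for the array.

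Aims and Objectives lists muscle gene expression among the primary determinants, which are secondary outcomes. Sample Size Determination uses muscle GLUT4 as the proxy for the secondary outcomes and sizes it between arms: "0.65 [SD 0.69] vs 0.01 [SD 0.69] AU for training vs control group".

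**The concern.** Each woman is measured before and after the 12 weeks, so the natural pairs are her two biopsies. A paired test on them asks whether expression moved over time. It does not ask whether expression moved more with exercise than without. Anything that moves expression in both arms, such as repeat biopsy, season or array batch, would be credited to training.

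The Discussion presents the array as a novel part of the study for finding pathways and genes, and the article's stated aim is causal. A before-after list cannot carry that aim. Confirming the same before-after change by RT-PCR would confirm the time effect, not an exercise effect.

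A second and smaller point is the unlogged scale. It can cost power where expression noise is multiplicative.

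**Working it through.** **1. The plan's own muscle sizing is a between-arm calculation.** Inputs from Sample Size Determination: difference 0.65 − 0.01 = 0.64 AU, SD 0.69, alpha .05 (taken as two-sided), power 80%.

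n per group = 2 × (1.960 + 0.842)² × 0.69² / 0.64² = 2 × 7.85 × 0.4761 / 0.4096 = 18.2, or 19 rounded up.

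The article states 18. Allowing for dropout, 18 / 0.9 = 20, as in "a dropout rate of 10% (2/20), 20 participants per group were selected". The figure reproduces to within one participant, and only as training versus control. A paired test does not deliver the contrast that was sized.

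**2. What the paired test does when both arms shift equally.** Let Δ be a shift common to both arms, in SDs of the pre-to-post change, with no exercise effect. The documents give no such shift, so Δ is assumed. The paired statistic follows a noncentral *t* with n − 1 df and noncentrality Δ√n. The article reports 20 exercise and 15 control completers. That all of them were arrayed is also an assumption.

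| Pairs tested | Δ = 0.25 | Δ = 0.5 |
|---|---|---|
| Exercise arm, n = 20: Δ√20 | 1.12 | 2.24 |
| Rejection at P<.05 | 19% | 56% |
| Both arms pooled, n = 35: Δ√35 | 1.48 | 2.96 |
| Rejection at P<.05 | 30% | 82% |
| Between-arm test of change | 5% | 5% |

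In the between-arm test the shift cancels (Δ − Δ = 0), so it keeps its nominal 5%.

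Testing each arm separately and comparing the verdicts does not solve this. At Δ = 0.5 the control test (15 pairs) rejects 44% of the time. The chance of significant in exercise but not in control is therefore 0.56 × (1 − 0.44) = 31%, again with no exercise effect.

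**3. FDR control does not repair it.** The q-value limits false claims about the hypothesis tested, which here is no change over time. A gene that shifts in both arms is a true positive for that hypothesis and a false one for exercise.

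**4. Scale.** Assumptions: lognormal noise, 20 pairs, between-person log2 SD 0.6, true change 1.5-fold. P<.001 stands in for a strict FDR cut.

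| Per-occasion log2 SD | Threshold | Logged | Unlogged | Loss (points) |
|---|---|---|---|---|
| 0.4 | P<.05 | 99.2% | 97.6% | about 2 |
| 0.6 | P<.05 | 83.4% | 74.2% | about 9 |
| 0.4 | P<.001 | 75.0% | 52.8% | about 22 |
| 0.6 | P<.001 | 26.5% | 12.9% | about 14 |

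**5. Price of the valid contrast.** In units of the SD of change, the standard error is √(1/20) = 0.224 for the paired test in the exercise arm. It is √(1/20 + 1/15) = 0.342 for the between-arm test, about 1.5 times larger. For an assumed effect of 0.9 SD with no control change, power at P<.05 on log2 signals is about 97% paired and 73% between arms.

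**The case against.** The strongest reply is that the paired test sits in a laboratory section, while the statistics section has a general between-arm ANOVA rule. Muscle gene expression is a secondary outcome, so that rule can be read to cover it. A journal article may also leave the list of arrayed samples to a fuller plan. This has force. A reader might infer that the array was run or tested in the exercise arm alone, or that control biopsies were ignored. The text says neither. What stands is that the paired test is the only method given specifically for the array, and it differs from the general rule. The two sections need to be reconciled.

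Other stronger readings also fail:

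- **The objectives require a control comparison for gene expression.** The control comparator is written into the first objective only, on insulin sensitivity and secretion. The objective on determinants names none. The conflict is with Proposed Statistics and the sizing, not with the objectives.
- **Unlogged signals let high-expressing genes dominate or create false positives.** The test is run gene by gene, so a gene's overall level does not matter. If pre and post are exchangeable under no change, the raw difference is symmetric about zero. The cost is power. The log rule is also conditional, so one unlogged analysis does not strictly breach it.
- **The trial's main conclusions are at risk.** The array is a discovery screen with planned validation, and the Discussion allows secondary data to serve as pilot data. The primary outcomes and their sample size are untouched.

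**Conclusion.** The point holds as a conflict to resolve, and it should be fixed. As stated, the array test cannot separate an exercise effect from a time effect, whichever pre/post samples were paired, and it does not match the between-arm rule or the between-arm sizing of the muscle marker.

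The rejection rates of 19% and 56% against 5% are illustrations. They rest on assumed common shifts of 0.25 and 0.5 SD and on 20 arrayed pairs. The documents do not show that any such shift occurred.

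The scale point is secondary. Under assumed lognormal noise the loss is about 2 to 9 points of power at P<.05 and 14 to 22 at P<.001. The documents give no SDs from which to fix its size.

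**What to change.** State which samples were paired, in which arm or arms, and whether control biopsies were arrayed. Reconcile the array paragraph with Proposed Statistics.

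If both arms were arrayed, take each woman's pre-to-post change in log2 signal, test the difference in change between arms for each gene (the arm-by-time contrast), and apply q<.05 to that contrast. Report within-arm changes as descriptive. This is a re-analysis of existing data.

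If control biopsies were not arrayed, re-analysis cannot supply the comparison. Label the array exploratory, and make the between-arm test at the planned RT-PCR stage using samples from both arms.

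The downside is precision. With 20 and 15 completers the between-arm contrast has a standard error about 1.5 times that of the paired test in the exercise arm, so fewer genes will pass. The change is made for validity, not power.
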